### **RECOVERY OF RENAL FUNCTION:**

Recovery of renal function will be defined as lack of need for continuous dialysis support, and will be classified as complete recovery, partial recovery, or no recovery.

Complete recovery of renal function will be defined as serum creatinine that is no more than 0.5 mg/dL greater than baseline; partial if the level remained above 0.5mg/dL above the baseline but not dialysis dependant. Patients who remain dialysis dependant at study completion or time of death will be categorized as having no recovery of renal function.

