#### **1. Improvement in Clinical Status**

- If a patient's condition improves (e.g. renal condition has improved to the extent that CRRT can be discontinued or hemodynamic status has improved so that the dialysis modality

can be changed from CRRT to IHD) treatment may be discontinued before the 168 hour treatment period. The decision to discontinue treatment based upon improvement in clinical status will be made by the Principal Investigator.

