## **APPENDIX D DEFINITIONS**

### **RENAL REPLACEMENT THERAPY (RRT) DEPENDANCY AT DAY 60**

RRT dependency at day 60 is defined as patient not receiving any form of intermittent or continuous renal replacement therapy at 60 days post enrollment in the study with no plans for additional intermittent or continuous renal replacement therapy.

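### Appendix D's renal recovery entry contradicts itself for survivors on intermittent haemodialysis, and its complete-recovery class has no dialysis-free condition

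*Protocol*

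**What the plan says.** The Appendix D entry on recovery of renal function contains four rules.

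- The opening definition: "Recovery of renal function will be defined as lack of need for continuous dialysis support". The same sentence says that recovery "will be classified as complete recovery, partial recovery, or no recovery".
- Complete: "Complete recovery of renal function will be defined as serum creatinine that is no more than 0.5 mg/dL greater than baseline".
- Partial: "partial if the level remained above 0.5mg/dL above the baseline but not dialysis dependant".
- No recovery: "Patients who remain dialysis dependant at study completion or time of death will be categorized as having no recovery of renal function".

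The RRT-dependency entry in the same appendix refers to "any form of intermittent or continuous renal replacement therapy". Section 7.2.1 lets study treatment end for clinical improvement, one example being that haemodynamics allow the modality that "can be changed from CRRT to IHD". Section 12.9 lists recovery of renal function among the exploratory outcomes, which are described by arm and not formally tested.

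**The concern.** The opening sentence and the last sentence use different tests. One asks whether continuous dialysis is still needed. The other asks whether the patient is dialysis dependent, whatever the modality. A patient moved from CRRT to intermittent haemodialysis without regaining kidney function passes the first test and fails the second, and Section 7.2.1 shows that the protocol expects such moves.

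The practical risk is a single recovered/not-recovered percentage. The pilot reported recovery in that form (Table 8), and Section 1.1 suggests that SCD may shorten maintenance dialysis, so such a figure would attract attention. Taken from the opening sentence, it would count survivors who still depend on intermittent dialysis as recovered. The trial is open-label, so a definition that allows two readings should be closed before outcome data are seen.

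**Working it through.** The question is one of wording, so the rules are applied one by one to a survivor who is dialysis dependent on intermittent haemodialysis (IHD) at study completion.

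| Rule in the entry | IHD, creatinine more than 0.5 mg/dL above baseline | IHD, creatinine within 0.5 mg/dL of baseline |
|---|---|---|
| Opening sentence, continuous read as a modality | recovered | recovered |
| Opening sentence, continuous read as ongoing | not recovered | not recovered |
| Complete | not met | met |
| Partial (requires no dialysis dependence) | not met | not met |
| No recovery | met | met |

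**Which reading of continuous is likelier.** The RRT-dependency entry sets continuous against intermittent. Appendix E gives Continuous as the CRRT modality. Section 5.1 describes the supplied machine as suited to continuous or intermittent therapies. All three name a modality, so that reading is the better supported one.

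**Where the classes overlap.** In the first patient column only the no-recovery class is met. In the second, both complete and no recovery are met. This overlap does not depend on the meaning of continuous: the partial class carries a dialysis-free condition and the complete class does not. Dialysis itself lowers creatinine, so the second column need not be empty. The protocol gives no figure from which its frequency could be computed.

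**How many survivors could be on dialysis.** Inputs: 172 randomised per arm and assumed 60-day mortality of 50% (control) and 35% (SCD), from Section 12.2; about 10% of AKI patients going on to chronic dialysis, from Section 1.1; pilot recovery of 24/24 survivors at day 60, from Table 8.

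- Expected control survivors: 172 × (1 − 0.50) = 86.
- Expected SCD survivors: 172 × (1 − 0.35) = 111.8.
- At the pilot's day-60 rate, non-recovery is 0/24, so 0 survivors are affected in either arm.
- If 10% applies to survivors: 86 × 0.10 = 8.6 and 111.8 × 0.10 = 11.2, or about 9 and 11.

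The two scenarios do not exclude each other, since Table 8 gives a lower confidence limit of 86.2% for the 24/24. Table 8 also does not state which definition of recovery it used, so the zero assumes that it meant free of all dialysis.

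**The case against.** The strongest reply is that no conflict reaches the reported classes. The opening sentence only introduces a three-way classification, and the last sentence assigns dialysis-dependent patients explicitly to no recovery. For most patients on intermittent dialysis this stands. A reader might infer that every such survivor is both recovered and not recovered, or that reported recovery would approach 100% in both arms. The document does not support either inference: the first holds only for the opening sentence under the modality reading, and the second requires an analyst to ignore the no-recovery rule altogether.

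It can also be said that continuous may mean ongoing, which removes the clash between the two sentences. The pilot's adverse event table (Table 7) does use the word for frequency. The reading is possible but runs against the protocol's usage for dialysis, and it leaves the gap in the complete class untouched. If ongoing was meant, the word still needs replacing.

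A larger count is tempting too. Applying the pilot's day-28 non-recovery, 7/26, gives 86 × 7/26 = 23.2 and 111.8 × 7/26 = 30.1 survivors. That is not a supported estimate, because the no-recovery rule applies at study completion or death and not at day 28, and the pilot does not state the dialysis modality of those 7 patients.

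Finally, no primary or secondary endpoint uses this definition. Dialysis status at day 60 has its own secondary endpoint, and duration of renal support has its own exploratory outcome. This stands and limits the weight of the point.

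**Conclusion.** The entry is inconsistent and should be corrected, as a minor point. Two defects hold:

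- The opening sentence, on the better-supported reading, contradicts the last sentence for survivors on intermittent haemodialysis. The exposure is to a yes/no figure drawn from it.
- The complete class overlaps the no-recovery class for dialysed patients with creatinine within 0.5 mg/dL of baseline.

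The 0 and the roughly 9 control and 11 SCD survivors are illustrations. The latter rest on the design mortality rates, on carrying a figure for AKI patients over to survivors, and on those patients being on intermittent dialysis. They size the group exposed to the first defect; only an unknown part of that group would fall into two classes. The trial's confirmatory conclusions are unaffected.

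**What to change.** In the recovery entry of Appendix D:

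1. Replace the criterion in the opening sentence (lack of need for continuous dialysis support) with: not receiving "any form of intermittent or continuous renal replacement therapy", and with no further renal replacement therapy planned. The second half matters because without it a patient between two intermittent sessions could count as free of dialysis.
2. Add the same dialysis-free condition to complete recovery, beside the creatinine threshold.
3. Write the condition out in full and do not refer to the RRT-dependency label. That entry currently defines dependency as its opposite, namely "not receiving any form of intermittent or continuous renal replacement therapy at 60 days", so a cross-reference would bring the inversion into the recovery outcome.

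The cost is a wording change in one entry, with no new visits or data. The day-28 and day-60 visits (Sections 6.5.2 and 6.5.3, Appendix I) list presence of renal replacement therapy without modality, which fits an any-form definition better than one resting on continuous dialysis. The absence of further planned therapy is already part of the RRT-dependency definition. A yes/no recovery figure could come out lower than under the present opening sentence.

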## 5.2. INCLUSION CRITERIA

1. A patient, or legal representative, has signed a written informed consent form.
2. Must be receiving medical care in an intensive care unit (e.g., ICU, MICU, SICU, CTICU, Trauma).
3. Age 18 to 80 years.
4. Females of child bearing potential who are not pregnant (confirmed by a negative serum pregnancy test) and not lactating if recently post-partum.
5. Must be receiving and tolerating CRRT for a minimum of 4 hours, but not longer than 24 hours.
6. Expected to remain in the ICU for at least 96 hours after evaluation for enrollment.
7. A clinical diagnosis of ATN due to hemodynamic or toxic etiologies. ATN is defined as Acute Kidney Injury occurring in a setting of acute ischemic or nephrotoxic injury with oliguria (average  $<20$  mL/hr) for  $>6$ – $12$  hours or: an increase in serum creatinine  $\geq 2$  mg/dL ( $\geq 1.5$  mg/dL in females) over a period of  $\leq 4$  days. (Note: Prerenal, hepatorenal, vascular, interstitial, glomerular, and obstructive etiologies are excluded on clinical or other diagnostic grounds.)
8. At least one non-renal organ failure (SOFA organ system score  $\geq 2$ ), as defined in Appendix A or presence (proven or suspected) of sepsis as defined in Appendix C.
9. All patients must be able to tolerate regional citrate anticoagulation.

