## 5.3. EXCLUSION CRITERIA

1. Irreversible brain damage based on available historical and clinical information.
2. Presence of a renal transplant at any time.
3. Non-renal organ transplantation within six month of screening.
4. Presence of preexisting advanced chronic renal failure (Stage 5) prior to this episode of AKI. Preexisting Chronic Renal Failure is defined as a baseline serum creatinine  $>2.5$  mg/dL (men) or  $>2.0$  mg/dL (women).
5. AKI occurring in the setting of burns, obstructive uropathy, allergic interstitial nephritis, acute or rapidly progressive glomerulonephritis, vasculitis, hemolytic-uremic syndrome, thrombotic thrombocytopenic purpura (TTP), malignant hypertension, scleroderma renal crisis, atheroembolism, functional or surgical nephrectomy, hepatorenal syndrome, cyclosporine or tacrolimus nephrotoxicity.
6. Metastatic malignancy which is actively being treated or may be treated by chemotherapy or radiation during the subsequent three month period after study therapy.
7. Chronic immunosuppression (e.g., HIV/AIDS, chronic glucocorticoid therapy  $>20$  mg/day prednisone equivalent on a chronic basis). The acute use of glucocorticoids is permissible.
8. Severe liver failure as documented by a Child-Pugh Liver Failure Score  $>12$  (see Appendix F).
9. Do Not Resuscitate Status (DNR).

10. Comfort measures only.
11. Patient is moribund or for whom full supportive care is not indicated.
12. Patient is not expected to survive 28 days because of an irreversible medical condition. (This is not restrictive to AKI, and may include situations such as the presence of irreversible brain damage, untreatable malignancy, inoperable life threatening condition, or any condition to which therapy is regarded as futile by the PI.)
13. Any medical condition that the Investigator thinks may interfere with the study objectives.
14. Physician refusal.
15. Patient is a prisoner.
16. Dry weight >150 kg.
17. More than one hemodialysis treatment during this hospital admission or prior to transfer from an outside hospital.
18. Platelet count <30,000/mm^3.
19. Concurrent enrollment in another interventional clinical trial. Patients enrolled in clinical trials where only measurements and or samples are taken (NO TEST DEVICE OR TEST DRUG USED) are allowed to participate.
20. Use of any other interventional drug or device within the previous 30 days.

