#### **6.3. BASELINE PERIOD**

The Baseline Period begins at randomization and ends at the start of the Observation Period. The following information will be recorded as close to the start of the Observation Period as possible. Data from standard of care tests may be used as baseline data, as long as it is captured within the time frames noted.

- **Demographic Data**
  - Date of birth
  - Gender
  - Race/ethnicity
- **Hospitalization Data**
  - Hospital Admission Date
  - Hospital Admission Diagnosis
  - ICU Admission Date
  - ICU Admission Diagnosis
- **Vital Signs/Physical Assessment**
  - Temperature
  - Blood Pressure, heart rate, body weight
  - EKG (**within 12 hours prior to the start of Observation Period**)
  - Sequential Organ Failure Assessment (SOFA Score)

- Physical Exam
  - Urine Output (previous 24 hours)
- **Clinical Laboratory Tests (within 12 hours prior to the start of Observation Period)**
  - CBC with differential
  - BUN/Creatinine
  - Na, K, Cl, HCO3, Ca, Mg, Ionized Ca, PO4
  - ALT, AST, LDH, Bilirubin, ALP, Total Protein, Albumin, Glucose
  - PT, PTT, INR
  - Haptoglobin
  - Urinalysis (if urine available)
- **Respiratory**
  - Status – Ventilator support (yes/no; date of intubation)
  - If on Vent: Mode, NO, FiO2, Settings (TV, PEEP, RR)
  - If on Vent with an arterial line: Arterial Blood Gas (12 hours prior to start of Observation Period)
  - If on Vent without an arterial line: Arterial Blood Gas (24 hours prior to start of Observation Period)
  - If not Vented: Supplemental oxygen requirements
- **Blood for Research**
  - Blood sample will be sent to an outside laboratory for testing of biomarkers such as IL6, IL10, Elastase, and GCSF.
- **Other (Event-driven)**
  - All the medications and blood products administered to the patient in the 24 hours prior to start of Observation Period.
  - Adverse Events occurring since randomization, unless directly related to screening procedure
  - Diagnostic/Therapeutic Procedures in the 24 hours prior to start of Observation Period.
  - Microbiology/culture data

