## **6.5. STUDY FOLLOW UP PERIOD**

### **6.5.1. POST END OF STUDY TREATMENT PERIOD**

This Study Follow Up period has been broken into seven 24 hour time periods. It starts when the patient has reached 168 hours in the observation period or when the patient meets the termination criteria outlined in section 7.2. It ends at 168 hours or until ICU discharge, whichever comes first. (Except for SOFA, net fluid balance and pressor use, which are followed until ICU discharge or Day 28, whichever comes first and microbiology/culture data which will be collected until hospital discharge or Day 60, whichever comes first.)

Record the following data daily in the Study Follow Up Period unless otherwise noted:

- **Vital Signs/Physical Assessment**
  - Blood pressure and heart rate
  - SOFA Score (record until ICU discharge or Day 28)
  - Physical Exam (first 24 hours only)
  - Body weight and temperature
  - EKG (first 24 hours only)
  - Urine Output (from previous 24 hours)
  - Net fluid balance (record until ICU discharge or Day 28 - from previous 24 hours)
- **Clinical Laboratory Tests (first 24 hours only)**
  - CBC with differential
  - BUN, Creatinine
  - Na, K, Cl, HCO3, Ca, Mg, Ionized Ca, PO4
- **Respiratory**
  - Status – Ventilator support (yes/no)
  - If on Vent: Mode, FiO2, Settings- TV, PEEP, RR
  - If on Vent with an arterial line: Arterial Blood Gas
  - If not Vented: Supplemental oxygen requirements
- **Renal Replacement Therapy status**
  - RRT status
- **Other (Event Driven)**
  - All the medications and blood products administered to the patient.
  - Pressor Usage (record until ICU discharge or Day 28)
  - Diagnostic/Therapeutic Procedures
  - Adverse Events
  - Microbiology/culture data (record until hospital discharge or Day 60)

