### **6.5.3. DAY 60 POST RANDOMIZATION**

This visit may be done via telephone call or office visit. Please record the following information on day 60 (+7 days) following randomization:

- Blood pressure, heart rate and temperature (if known)
- Presence of mechanical ventilation (since last visit)
- Presence of renal replacement therapy (since last visit)
- ICU discharge date
- Hospital discharge date
- Adverse events (since last visit)
- Serum creatinine (if an office visit takes place)
- SF36v2 Quality of Life Questionnaire

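### Appendix D grades renal recovery against an undefined baseline creatinine; the only one scheduled for recording is an AKI-phase value, so partial recovery can be graded as complete

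*Protocol*

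**What the plan says.** Under Recovery of Renal Function, Appendix D sets three grades. The rule for the top grade is: "Complete recovery of renal function will be defined as serum creatinine that is no more than 0.5 mg/dL greater than baseline". The middle grade is "partial if the level remained above 0.5mg/dL above the baseline but not dialysis dependant". For the lowest: "Patients who remain dialysis dependant at study completion or time of death will be categorized as having no recovery of renal function". The entry names neither the baseline nor the time of the later creatinine.

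The protocol uses the word baseline in two senses:

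- Section 6.3: "The Baseline Period begins at randomization and ends at the start of the Observation Period". Creatinine is among the laboratory tests due in the 12 hours before Observation start. Inclusion criterion 5 puts the patient on CRRT by then: "Must be receiving and tolerating CRRT for a minimum of 4 hours, but not longer than 24 hours".
- Exclusion 4 (section 5.3), which concerns the state before the current AKI episode: "Preexisting Chronic Renal Failure is defined as a baseline serum creatinine" above a sex-specific limit.

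At Day 60 (section 6.5.3) the item reads "Serum creatinine (if an office visit takes place", and a telephone call may replace the visit. Section 6.5.2 says the same for Day 28.

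Section 12.9 lists recovery of renal function among the exploratory outcomes, to be described by arm without testing.

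**The concern.** Complete recovery ordinarily means a return to near the patient's own level before the illness. Anyone who follows the protocol's data lists will have only one number labelled baseline, and it comes from an injured kidney. Measured against that number, a survivor off dialysis with a clearly raised creatinine can count as completely recovered.

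An SAP may choose the reference, but it cannot analyse a value that the protocol did not have recorded.

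The split between complete and partial could matter. Table 8 reports renal recovery in 24 of 24 evaluable survivors at Day 60 in the US pilot, without giving the definition there. If dialysis freedom is again close to its ceiling, the creatinine grading is the part of this outcome that could still separate the arms.

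The late creatinine is a second weakness. Whether it exists depends on the type of contact, so survivors with a value are a selected group.

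**Working it through.** The plan gives no figure to reproduce. The check traces each creatinine and then compares the two readings of the rule.

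**Step 1. Which creatinine values are scheduled**

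- Before AKI: needed to judge exclusion 4, but not listed in section 6.3 or Appendix G.
- Baseline Period: within 12 hours before Observation start.
- Observation Period: daily, up to 168 hours (section 6.4).
- After end of treatment: in the first 24 hours only (section 6.5.1, Appendix H).
- Days 28 and 60: only at an office visit (sections 6.5.2 and 6.5.3, Appendix I).

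**Step 2. The cut-off under each reading, no washout**

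Cut-off for complete recovery = baseline + 0.5 mg/dL. Assume a pre-AKI creatinine of 1.0 mg/dL (not in the documents). The minimum qualifying rise is 2 mg/dL for men and 1.5 mg/dL for women (inclusion 7, Appendix B).

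- Pre-AKI reading, either sex: 1.0 + 0.5 = 1.5 mg/dL.
- AKI-phase reading, man: (1.0 + 2.0) + 0.5 = 3.5 mg/dL.
- AKI-phase reading, woman: (1.0 + 1.5) + 0.5 = 3.0 mg/dL.

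Without washout the gap equals the rise, whatever pre-AKI value is assumed: 2.0 mg/dL for the man and 1.5 mg/dL for the woman. A patient who enters above the minimum rise has a larger gap.

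**Step 3. Allowing for CRRT washout**

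One-compartment model: C(t) = Css + (C0 − Css)·exp(−Kt/V), with Css = G/K. Assumptions, none from the documents: V 36 to 54 L, clearance K 1.5 to 2.5 L/h, generation G 1 g/day (41.7 mg/h), and C0 = 3.0 mg/dL at CRRT start. Time on CRRT is t = 4 to 24 h, as in inclusion 5.

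- Most washout (V = 36, K = 2.5, t = 24): Css = 41.7/2.5/10 = 1.67 mg/dL; exp(−60/36) = 0.19; C = 1.67 + 1.33 × 0.19 = 1.92 mg/dL. Cut-off: 2.42 mg/dL.
- Least washout (V = 54, K = 1.5, t = 4): Css = 41.7/1.5/10 = 2.78 mg/dL; exp(−6/54) = 0.89; C = 2.78 + 0.22 × 0.89 = 2.98 mg/dL. Cut-off: 3.48 mg/dL.

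The man's cut-off is therefore about 2.4 to 3.5 mg/dL against 1.5, an excess of about 0.9 to 2.0 mg/dL.

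**Step 4. One patient, two grades**

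This man, off dialysis with a later creatinine of 2.4 mg/dL, is partial on the pre-AKI reading (2.4 > 1.5) and complete on the recorded value even at the most washout (2.4 < 2.42).

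**Step 5. Entry by oliguria**

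This route requires no minimum creatinine rise, so the shift for these patients cannot be bounded from the protocol.

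**The case against.** The strongest reply is that Appendix D never says its baseline is the Baseline Period value. Exclusion 4 uses the term for a pre-AKI value, and on that reading the rule is sensible. The choice could be left to the SAP, and sites must look at the pre-AKI value for eligibility anyway. This stands in part: the defect is an undefined reference, not a stated wrong one. But the protocol nowhere lists the pre-AKI value for recording, so the sensible reading lacks its data.

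A reader might also infer more than the text supports:

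- *Unrecovered kidneys are counted as completely recovered.* They are not: dialysis-dependent patients are no recovery by rule. The possible error is partial graded as complete.
- *A missing late creatinine produces a complete recovery.* It leaves the patient ungraded.
- *Creatinine after baseline depends entirely on an office visit.* That holds only for Days 28 and 60. It is also taken daily to 168 hours and in the next 24 hours, though those values come during or just after study therapy and say little about recovery. SOFA, recorded until ICU discharge or Day 28, has a renal component, but it is banded and may rest on urine output.
- *The baseline value is always taken on CRRT.* With under 12 hours of CRRT at Observation start, the 12-hour window can reach a pre-CRRT standard-of-care value. That is still an AKI value, without washout, so the cut-off is no stricter.
- *Nearly every dialysis-free survivor would be complete.* The documents give no creatinine distribution from which to derive this.

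**Conclusion.** The point holds as a defect of definition and data collection. The complete/partial grading has no stated reference, and the only baseline creatinine scheduled for recording is from the AKI phase. If it is used, the cut-off for a man with pre-AKI creatinine 1.0 mg/dL entering at the minimum rise is too high by up to 2.0 mg/dL, or by about 0.9 to 2.0 mg/dL under the assumed washout. For a woman it is too high by up to 1.5 mg/dL before washout. These figures rest on the assumed pre-AKI value, entry by the creatinine route at the minimum rise, and the washout inputs. How many patients would change grade cannot be estimated.

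Separately, dialysis-free survivors reached only by telephone may have no late value to grade.

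A reader might take this as a threat to the trial's renal endpoint. It is not one: the secondary endpoint is RRT dependency at day 60, which does not use creatinine. The primary endpoint and all four secondary endpoints are unaffected. The correction is still worth making, because the pre-AKI value is best captured at screening.

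**What to change.** - In Appendix D, define baseline for this outcome as the pre-AKI serum creatinine used to judge exclusion 4, and add that value to the baseline CRF and to the lists in section 6.3 and Appendix G.
- Assign complete or partial only where an off-dialysis creatinine exists at a stated time point, Day 60.
- Report all other survivors only as dialysis-free or not, and show the number ungraded by arm.

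The last in-hospital creatinine is a less suitable substitute for Day 60: its timing varies with length of stay, which could itself differ between arms.

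The cost is one CRF field, for a value already needed at screening, and a short addition to Appendix D. The complete-recovery rate will be lower and some patients will stay ungraded. Showing the ungraded number discloses the selection by visit type but does not remove it. Sample size, alpha and the analyses of the primary and secondary endpoints do not change.
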